## 5.3 Dosage and Administration of IP

Subjects will be instructed to take the investigational product as 5 capsules in the morning with food on a daily basis for 168 days.

## 5.4 Storage

All study products will be stored in a secure location at room temperature protected from heat and direct light. Only the Investigator or designated members of the research team will have access to the study products.

## 5.5 IP Accountability

NDI will maintain records pertaining to the IP received from the Sponsor, the date the IP was received, and the disposition of the IP (e.g., dispensing and use by study participants), or if unused, the return of the IP to the Sponsor or other mutually agreed upon disposition (e.g. destruction).

## 5.6 Blinding

The investigational product and comparator product will be similar in shape and size. Both products will be labelled in a similar manner and will only be differentiated by a randomization code to ensure the study is double-blind.

## **5.7 Unblinding**

Unblinding should not occur except in the case of emergency situations. In the event that a serious adverse event occurs, for which the identity of the investigational product administered is necessary to manage the patient's condition, the treatment emergency code for that participant may be broken and the investigational product identified. The sponsor must be notified of any unblinding within 24 hours. Details of patients who are unblinded during the study will be included in the final report.

Unblinding of the data will not occur until after database lock to ensure integrity of the study data.

## **6 ASSESSMENT OF EFFICACY**

All assessments of efficacy will be made on blood collected during the clinical study period.

### **6.1 Primary Endpoints**

The primary endpoints are red blood cell EPA and DHA after 6 months (24 weeks) of supplementation and serum phospholipid fatty acid analysis after 1 month of supplementation.

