|                             |                                                                                                                                                                                                                                                                                                                                                                                                                                                                                                                                                                                                                                                                                                                                            |
|-----------------------------|--------------------------------------------------------------------------------------------------------------------------------------------------------------------------------------------------------------------------------------------------------------------------------------------------------------------------------------------------------------------------------------------------------------------------------------------------------------------------------------------------------------------------------------------------------------------------------------------------------------------------------------------------------------------------------------------------------------------------------------------|
| Statistical Methods: | 
Numerical efficacy endpoints will be formally tested for significance by analysis of covariance. The dependent variable will be the post-baseline value; the factor of interest will be the treatment group (product) and value at baseline (usually visit 2, except for some laboratory tests [e.g. lipid profile and safety parameters] where baseline is visit 1) will be the covariate.
 
The proportion of adverse events will be compared between groups using Fisher's Exact test or Chi-square test, as appropriate.
 
All calculations and analyses will be performed using SAS version 9.2 or higher. For all statistical inferences, the tests will be performed at the two-sided, 0.05 level of significance.
 |

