## **2 TRIAL OBJECTIVES AND PURPOSE**

### **2.1 Primary Objectives**

The primary objective of this clinical trial is to assess the relative efficacy of a 90% rTG Ultimate Omega® in comparison to another TG form of fish oil (Meg-3™, DSM Nutritional Products, Ltd.) Omega-3 by assessing the percentage of EPA and DHA in red blood cells after 6 months of supplementation and serum phospholipid fatty acid profile after 1 month of supplementation.

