### **2.1 Secondary Objectives**

Secondary objectives include the red blood cell fatty acid profile after 12, 16 and 24 weeks of supplementation and lipid profile (total cholesterol, LDL-C, HDL-C and triglycerides) after 6 months (24 weeks) of supplementation.

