## **8.1 Planned Interim Analysis**

When approximately 100% of participants have completed Visit 3 (Day 28), an interim analysis to determine changes in serum phospholipid fatty acids will be performed by research staff not involved in the conduct of the clinical trial.

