## **8.4 Statistical Methods**

An effectiveness analysis based on the intent-to-treat population will be performed for all efficacy outcomes. Continuous variables will be presented as means with standard errors of the mean (SEM). Categorical variables will be shown as frequencies or proportions. Numerical efficacy endpoints will be

formally tested for significance by analysis of covariance. The dependent variable will be the post-baseline value; the factor of interest will be the treatment group (product) and value at baseline (usually visit 2, except for some laboratory tests [e.g. lipid profile] where baseline is visit 1) will be the covariate.

The ANCOVA approach differs from the simpler approach of comparing changes from baseline between products in that the ANCOVA adjusts for baseline in a more sophisticated way than simply subtracting it from the end of study value. The adjustment allows the ANCOVA to compensate for regression to the mean, floor effects, and other ways that the baseline value could influence change from baseline.

Where values being summarized as significantly non-normally distributed, as assessed by the Anderson-Darling test, a non-parametric test, such as the Wilcoxon or Mann-Whitney U test will be used.

A within-group analysis, if warranted, may be performed using a Student's paired samples t-test or Wilcoxon sign rank test.

All calculations and analyses will be performed using SAS version 9.2 or higher. For all statistical inferences, the tests will be performed at the two-sided, 0.05 level of significance.

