#### **10.2 Incentives and Benefits for the Subjects**

There are no direct benefits from participating in this study. The risks associated with this study are low. If the study demonstrates efficacy, such as bioequivalence or superiority to the comparator product, Meg 3™, others could possibly benefit from using a high purity triglyceride form of fish oil, specifically Ultimate Omega®.

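### Section 6.1 names at least three primary variables, section 8.4 tests each at two-sided 0.05, and the protocol gives no rule for combining them

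*Protocol*

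**What the plan says.** Protocol section 6.1 reads: "The primary endpoints are red blood cell EPA and DHA after 6 months (24 weeks) of supplementation and serum phospholipid fatty acid analysis", with the serum measure taken after one month. The primary objective in section 2.1 calls the serum component the "serum phospholipid fatty acid profile after 1 month of supplementation". Neither section names a fatty acid, or a sum of fatty acids, for serum.

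The synopsis gives the test: "Numerical efficacy endpoints will be formally tested for significance by analysis of covariance", with baseline as covariate. Section 8.4 gives the scope, "An effectiveness analysis based on the intent-to-treat population will be performed for all efficacy outcomes", and the level: "For all statistical inferences, the tests will be performed at the two-sided, 0.05 level of significance".

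The protocol does not say how the primary results combine into a conclusion. The nearest it comes is section 10.2, "If the study demonstrates efficacy, such as bioequivalence or superiority to the comparator product", which is tied to no endpoint. The serum endpoint is read first. For the point at which about all participants have passed Day 28, section 8.1 plans the following: "an interim analysis to determine changes in serum phospholipid fatty acids will be performed by research staff not involved in the conduct" (meaning this trial's conduct). Section 11 sends an interim report to the sponsor at that stage.

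The secondary objective covers the "red blood cell fatty acid profile after 12, 16 and 24 weeks of supplementation". Section 6.2 lists RBC EPA and DHA as secondary at weeks 12 and 16 only.

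**The concern.** With several primary variables, the stated 0.05 is the error rate of each test. It is the error rate of the trial's primary conclusion only if a rule ties the tests together, and none is stated. Two products with identical effects would then show a nominally significant primary difference more often than 1 time in 20.

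The open serum definition adds to this. With no component named in advance, the serum conclusion could rest on whichever fatty acid happens to differ. The two products also differ in labelled EPA and DHA per capsule (section 1.2), so the choice of variable that carries the claim matters.

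**Working it through.** **The plan's own figure.** The protocol states no familywise error rate and no power. Its one derivable figure is the sample size in section 8.2: 24 completers per group with 20% attrition gives 24 / (1 - 0.20) = 30 per group, as stated.

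**Inputs from the protocol.** Two-sided 0.05 for each test (8.4); primary variables RBC EPA, RBC DHA and serum phospholipid fatty acids (6.1); 24 completers per group (8.2).

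**Assumptions.** The protocol fixes neither the number of tests k nor their correlation. I take:
- k = 2: EPA and DHA in RBC read as one combined percentage, plus one serum measure.
- k = 3: RBC EPA, RBC DHA and one serum measure.
- k = 4: EPA and DHA separately in each matrix.
- A common correlation between test statistics from 0 to 0.8.

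**Any false positive, either direction.** For independent tests the chance is 1 - (1 - 0.05)^k:
- k = 2: 1 - 0.95^2 = 9.75%
- k = 3: 1 - 0.95^3 = 14.3%
- k = 4: 1 - 0.95^4 = 18.5%

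For correlated tests I simulated equicorrelated normal statistics with no true difference on any variable:

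| k | correlation 0 | 0.5 | 0.8 |
|---|---|---|---|
| 2 | 9.75% | 9.0% | 7.8% |
| 3 | 14.3% | 12.5% | 9.9% |
| 4 | 18.5% | 15.6% | 11.3% |

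Repeat simulations moved these values by about 0.1 percentage point.

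**False positives favouring one named product.** The nominal rate in one direction is 2.5% per test, so for independent tests the chance is 1 - 0.975^k:
- k = 3: 7.3% (4.9% at correlation 0.8)
- k = 4: 9.6% (5.7% at correlation 0.8)

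These are about half of the two-direction rates, but still above 2.5%.

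**Cost of splitting alpha.** With 24 per group, a two-sample t-test and 80% power, the detectable difference is 0.826 SD at 0.05 and 0.915 SD at 0.025. No gain from baseline adjustment is counted.

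**The interim.** The Day 28 analysis tests the serum endpoint at its own time point. It is one member of the family counted above and not a repeated look at the same variable, so it adds nothing to k.

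**Week-24 RBC data.** Section 6.1 makes RBC EPA and DHA at week 24 primary. The secondary objective in 2.1 includes the RBC profile at week 24, whereas 6.2 stops at week 16. The objective and the endpoint list therefore differ on whether week-24 RBC data have a secondary role.

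**The case against.** **Multiplicity belongs in the SAP.** A SAP may well exist, and it commonly holds the testing procedure and the list of serum components. But the protocol does not leave the level open: it sets 0.05 for all inferences and lists the primary endpoints itself. A SAP that controlled the error would have to override that text.

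**No success rule is stated.** A reader might infer that a win on any one endpoint suffices to claim superiority. The protocol does not say so; it gives neither an any-one rule nor an all-must-succeed rule. If all had to be significant, there would be no inflation. This stands as a limit: the rates above are conditional on an any-one reading, which the text permits but does not declare.

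**The rates are not the risk of a false claim for the sponsor's product.** Correct. They count both directions, and about half of each favours the sponsor's product.

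**The whole profile.** A reader might count every serum fatty acid as a primary test and quote a much larger error, for example 68% for 22 independent tests. That needs 20 serum fatty acids, a count the protocol does not give, and independence, which percentages within one profile cannot have. The documents support only that the error would be higher than for three or four tests.

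**The primary and secondary sets overlap.** A reader might say the same endpoint is both primary and secondary. The secondary objective concerns the RBC profile, the primary concerns EPA and DHA, and 6.2 already omits week 24. Only the wording of the objective needs aligning.

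**The trial is exploratory.** It is Phase II, section 8.2 calls it investigative, and no formal sample size was calculated. That lessens the consequences. But it names primary endpoints, tests them formally and contemplates a superiority conclusion.

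**Conclusion.** Wrong as written. The protocol fixes two-sided 0.05 for each of at least three primary variables, leaves one of them without a named component, and states no rule for combining them.

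If any one difference is taken as a positive primary result, the chance of at least one false positive in either direction is about 10-14% for three tests and 11-19% for four, and 8-10% on the narrowest reading of two. The ranges rest on assumed correlations from 0.8 to 0 and on the assumed number of tests. Every case considered exceeds 5%.

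**What to change.** **Name the variables.** In sections 2.1, 6.1 and 8.4, name one primary variable per matrix, for example EPA+DHA as a percentage of total fatty acids in RBC at week 24 and in serum phospholipid at week 4.

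**Control 0.05 across these two only.** Either of these will do:
- Holm: the smaller p-value is tested at 0.025 and, if it is significant, the other at 0.05. Because serum is read first, it is tested at 0.025 at the interim. RBC is then tested at 0.05 if serum succeeded and at 0.025 if not. If serum missed 0.025 but RBC succeeds, serum is judged again at 0.05.
- A prespecified order, each tested at 0.05, the second only if the first is significant.

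**Everything else.** Report EPA and DHA separately, other fatty acids, other visits and lipids as secondary or exploratory, with no confirmatory claim. Testing EPA and DHA as follow-ups to a significant sum, while Holm also passes that alpha to the other matrix, spends it twice. In a simulated case with a large true serum EPA effect, that gave a familywise error of about 7% with the components at 0.025 and 9% at 0.05. Separate claims need a procedure that does not reuse alpha.

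**Align the secondary objective** in 2.1 (RBC profile at week 24) with 6.2 (weeks 12 and 16 only).

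**Cost.** Wording only, with no extra participants, visits or blood samples. With 24 completers per arm, the difference detectable at 80% power rises from 0.83 to about 0.92 SD for an endpoint tested at 0.025. A fixed order avoids that loss, but the second endpoint cannot be claimed if the first fails.

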### **6.2 Secondary Endpoints**

Secondary outcomes include the red blood cell EPA and DHA after 12 and 16 weeks of supplementation and lipid profile (total cholesterol, LDL-C, HDL-C and triglycerides) after 6 months (24 weeks) of supplementation.

## **7 ASSESSMENT OF SAFETY**

Adverse events will be reviewed at each study visit. Additionally, vital signs, body weight, BMI will be used as measures of product safety. Blood will be collected prior to and after 6 months of supplementation for analysis of safety parameters (hematology and clinical chemistry).

### **7.1 Adverse Events (AEs)**

Health Canada's NNHPD define an adverse event as "any adverse occurrence in the health of a clinical trial subject who is administered an NHP that may or may not be caused by the administration of the NHP, and includes an adverse reaction, a serious adverse reaction and a serious unexpected adverse reaction". NNHPD defines an adverse reaction as "a noxious and unintended response to an NHP that occurs at any dose used or tested for the diagnosis, treatment or prevention of a disease or for modifying an organic function". Adverse events are further defined in ICH Guideline E2A that "an adverse event can therefore be any unfavorable and unintended sign (including an abnormal laboratory finding, for example), symptom or disease temporally associated with the use of a medicinal product, whether or not considered related to the medicinal product." Pre-existing conditions which worsen during a study are to be reported as AEs.

### **7.1.1 AE Reporting**

AE reporting processes will be carried out in compliance with the protocol, the governing Institutional Review Board (IRB), and government regulations.

AEs are intended to be volunteered by subjects or observed by the investigator. All AEs are to be recorded on appropriate Case Report Forms (CRFs). During the study, subjects should record any adverse effects in their diary. At each visit the subject will be asked "Have you experienced any difficulties or problems since I saw you last"? Any adverse events (AEs) will be documented in the study record and will be classified according to the description, duration, intensity, frequency, and outcome. The Principal Investigator will assess any AEs and decide causality.

### **7.1.2 Unexpected Adverse Reaction**

An unexpected adverse reaction is an adverse reaction, the nature and severity of which is not consistent with the applicable product information (e.g., Investigator's Brochure for an unapproved investigational product or package insert/summary of product characteristics for an approved product).

### **7.1.3 Plan for Grading Adverse Events:**

The following 3-point scale will be used in grading the severity of adverse events noted during the study:

- Mild: Awareness of event but easily tolerated
- Moderate: Discomfort enough to cause some interference with usual activity
- Severe: Inability to carry out usual activity

### **7.1.4 Plan for Attribution of Adverse Events:**

Adverse events will be monitored for each subject participating in the study and attributed to the study procedures / design by the principal investigator according to the following categories:

- Definite: An adverse event that followed a reasonable temporal sequence from administration of the study drug; followed a known response pattern to the study drug; when appropriate to the protocol, was confirmed by improvement after stopping the study drug (positive de-challenge) and by reappearance of the reaction after repeat exposure (positive re-challenge); and could not be reasonably explained by known characteristics of the subject's clinical state or by other therapies.
- Probable: An adverse event that followed a reasonable temporal sequence from administration of the study medication; followed a known response pattern to the study medication; when appropriate to the protocol, was confirmed by improvement after de-challenge; and could not be reasonably explained by the known characteristics of the subject's clinical state or by other therapies.

- Possible: An adverse event that followed a reasonable temporal sequence from administration of the study drug and followed a known response pattern to the study medication but could have been produced by the subject's clinical state or by other therapies. De-challenge information is lacking or unclear.
- Not related: An adverse event for which sufficient information existed to indicate that the etiology was unrelated to the study drug. Two or more of the following variables applied:
  - a. The adverse event did not follow a reasonable temporal sequence after administration of the study drug.
  - b. The adverse event was readily explained by the subject's clinical state or other therapies.
  - c. Negative de-challenge – the adverse event did not abate upon dose reduction or cessation of therapy (assuming that it was reasonable to expect abatement of the adverse event within the observed interval).

#### **7.1.5 Plan for Determining Seriousness of Adverse Events:**

In addition to grading the adverse event, the principal investigator (or qualified designate) will determine whether the adverse event meets the criteria for a Serious Adverse Event (SAE). An adverse event is considered serious if it:

- is life-threatening OR
- results in in-patient hospitalization or prolongation of existing hospitalization OR
- results in persistent or significant disability or incapacity OR
- results in a congenital anomaly or birth defect OR
- results in death OR
- based upon appropriate medical judgment, may jeopardize the subject's health and may require medical or surgical intervention to prevent one of the other outcomes listed in this definition (Examples of such events are intensive treatment in an emergency room or at home for allergic bronchospasm; blood dyscrasias or convulsions that do not result in hospitalization; or the development of drug dependency or drug abuse) OR
- adversely affects the risk/benefit ratio of the study

An adverse event may be graded as severe but still not meet the criteria for a Serious Adverse Event. Similarly, an adverse event may be graded as moderate but still meet the criteria for an SAE. It is important for the principal investigator to consider the grade of the event as well as its "seriousness" when determining whether reporting to the REB is necessary.

### 7.1.6 Serious Adverse Event (SAE) Reporting

SAE reporting processes will be carried out in compliance with the protocol and the governing REB. Notification of any serious adverse events must be made in writing to the study sponsor within 24 hours of the Principal Investigator learning of the event ([name], [[contact]](mailto:[contact])). All SAEs must also be recorded on an AE CRF. The REB will be notified by Nutrasource Diagnostics Inc. of all SAEs and unexpected adverse reactions as required by the governing REB.

Nutrasource Diagnostics Inc. will notify the therapeutic products directorate (TPD) via [contact]) or electronic submission to the Canada Vigilance database of all serious adverse or unexpected adverse reactions on behalf of Nordic Naturals using the CIOMS form as follows:

- a. If it is neither fatal nor life threatening, within 15 days after the day on which the sponsor becomes aware of the information; and
- b. If it is fatal or life threatening, within seven days after the day on which the sponsor becomes aware of the information.
- c. Where it is fatal or life-threatening, immediately where possible and, in any event, within 7 days after becoming aware of the information. Within 8 days after having informed Health Canada, submit as complete as possible, a report which includes an assessment of the importance and implication of any findings (if this was not already part of the initial report).

As part of the CIOMS form, a number unique to the AE will be generated. Any follow-up reports must contain this number followed by -02, -03, etc. for each follow-up report. If the blind was broken for the SAE, this must be recorded in the CRF, communicated to the Sponsor, and the identity of the investigational treatment included in the SAE report to Health Canada and the REB. If the blind is maintained, a follow-up report should be submitted to the Health Canada and the REB once the blind has been broken for the study. A record of successful transmission of SAE reports and follow-ups to the REB and Health Canada must be maintained in the Trial Master File (TMF).

An initial written report of any SAE will be submitted by the Investigator to the Sponsor within three business days of occurrence or notification of occurrence. Any necessary follow-up reports will be submitted within a reasonable time thereafter.

The follow-up report will give full details of the experience, including an assessment of the relationship to the test article(s) and will be sent to the Sponsor promptly. When contacting the Sponsor regarding SAEs, site personnel should be prepared to provide as much of the following information as is available at the time:

- Subject's initials and subject number
- Investigator's name and center number
- Protocol title and number
- Subject's date of birth, gender, and race
- Test article(s), date(s) of administration, if blinded, please indicate
- Concomitant medication(s): dose, route, duration of treatment, date of last dose
- Information regarding the AE:
  - Description
  - Dates the event began and ended

- Whether the experience resulted in death or was life-threatening
- Whether hospitalization was required or prolonged
- Any treatment(s) required
- Outcome(s) of treatment(s)
- Investigator's determination of relationship to IP

